#### Secondary statistical analysis

The main secondary analyses will consist of the comparisons between arms for individual components of the composite, that is, all-cause mortality, all-cause hospitalisation rate, proportion with >40% eGFR reduction from baseline, new development of ESRD and proportion with absolute HbA1C reduction >0.5% (>5.5 mmol/mol). Secondary outcomes as listed in the study outcomes above will also be analysed, treating these as exploratory analyses.

All analyses will be on an intention-to-treat basis.

A full statistical analysis plan will be published prior to data-lock.

#### Qualitative data analysis

Interview transcripts will be checked for accuracy, anonymised, and then imported into QSR NVivo software to aid analysis and management of data. Thematic analysis will be used to identify and analyse patterns and themes across the dataset.^22^ Analysis will take place concurrently with the data collection process to enhance the rigour and trustworthiness of the findings. Additional techniques to enhance trustworthiness will be put in place, including independent coding triangulation and group-based data analysis critique and data interpretation sessions with the rest of the research team and the study’s patient and public involvement (PPI) group.

#### Health economics analysis

A model-based cost-effectiveness analysis of the *iDiabetes (guideline support*) and *iDiabetesPlus* arms versus the *usual diabetes care* arm will be conducted. The cost per complication avoided and Quality-Adjusted Life Year gained (the standard health economic utility measure) for each strategy will be predicted by incorporating the study data into an existing diabetes simulation model.^23^,^25^ To estimate the resource implications of introducing the iDiabetes platform at scale in NHS Scotland, a budget impact analysis will be conducted. This will assess whether the recommendations from the cost-effectiveness analysis model are affordable to NHS Scotland.

The DCE data will be used to (1) assess the relative importance of attributes in the delivery of personalised diabetes care; (2) predict patient uptake of alternative treatment plans and (3) estimate benefit-risk trade-offs associated with the risk of adverse outcomes. The DCE data will complement the cost-effectiveness analysis evidence, ensuring that the iDiabetes platform is valued by service users.

#### Ancillary analyses

Exploratory objectives will be evaluated through dedicated substudies. The methodology for analysis will be disseminated through the publications of each substudy.

### Sample size calculations

#### Simulation of power for composite outcome

For the composite primary outcome, no standard method has yet been developed for sample size estimation, but Zhang and Jeong have developed an R-package which simulates the cluster WR (cWR), which has been adapted for this study design.^26^ The function uses two outcomes—mortality rate and non-fatal hospitalisation. As the primary endpoint in this study is a composite of four outcomes, it will have greater power than that estimated by the simulation as power increases with the number of outcomes in the composite. In the simulations using the R-package developed by Zhang and Jeong, 10% of the planned iDiabetes study population size was used so that there were 60 clusters and 2400 patients, that is, 40 per cluster and 80 person-years. The gamma frailty parameter beta for shape and rate was set at 20, which is equivalent to an intra-cluster correlation (ICC)=0.05. The results of 500 simulations gave the proportion of statistically significant results (p<0.05) as 413 so power was 82.6% to detect a mean WR=1.20. Hence power is excellent using the total number of clusters (60) and only with 10% of the proposed study population size.

#### Power for individual outcomes

In addition, power was also estimated for the individual components of the composite. Difference in Poisson rate or incidence rate ratio was used in these calculations as this is similar to HR in a time-to-event analysis, especially with low censoring and mortality. For example, for hospitalisation with 40 clusters, 81% power is achieved to detect a difference in Poisson rate of 8% or more (45% reduced to 37%) assuming an ICC=0.03 and alpha=0.05.

All individual outcome sample sizes were estimated using PASS 2023 Sample Size and Power Analysis Software.

#### Qualitative study sampling

A purposeful, maximum variation sampling strategy will be employed. Initial sampling criteria will account for characteristics relating to the setting, including the type of intervention (*iDiabetes (guideline support*) or *iDiabetesPlus* settings), practice size (<6000, 6000+) and deciles of deprivation^1^,^10^; and participants, including staff (eg, seniority, professional groups and roles) and patients (age, T1D or T2D) to maximise variation. Sampling criteria will be subsequently refined as data collection and data analysis progress. The estimated overall sample size is 20–25 primary care staff and 38–46 patients. Recruitment will take place in primary and secondary care iDiabetes clinical visits and via recruitment adverts on the iDiabetes and MyDiabetesMyWay websites. If further recruitment avenues are required, the Scottish Health Research Register and Biobank [SHARE] will be used to identify and approach potential participants. Healthcare professionals will be invited via professional care networks and internal email lists.

#### Discrete Choice Experiment

As with the qualitative study, a purposeful, maximum variation sampling strategy will be employed. Think-aloud interviews will be held until the saturation point is reached (when two consecutive interviews yielded no new information regarding survey improvements).^27 28^ It is anticipated that saturation will be reached with 20 interviews. Minimum sample size for the DCE survey is calculated using Louviere’s formula for choice proportions. Given a baseline choice probability of 33% (as each choice will involve three options), an accuracy level of 90%, a CI of 95% and eight choice tasks per respondent, we require 234 respondents.^29^ We will explore preference heterogeneity using flexible logit models; therefore, a minimum of 5000 individuals will be sent an email link to the survey. Assuming a response of 30%, this will allow for subgroup analysis (how preferences differ according to the characteristics of respondents). We will recruit at least 234 individuals to pilot the survey.

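### The discrete choice experiment minimum of 234 respondents does not follow from the inputs given for it; the usual form of the named formula gives 98

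*Protocol article*

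**What the plan says.** The subsection on the Discrete Choice Experiment, under Sample size calculations in the protocol article, sets out a short derivation. It names the method: "Minimum sample size for the DCE survey is calculated using Louviere’s formula for choice proportions". It takes a baseline choice probability of 33%, because each choice offers three options. The remaining inputs and the result follow in one clause: "an accuracy level of 90%, a CI of 95% and eight choice tasks per respondent, we require 234 respondents".

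Two further statements bear on the figure. For preference heterogeneity and subgroup analysis, "a minimum of 5000 individuals will be sent an email link to the survey", with an assumed response of 30%. The subsection then ends on the pilot: "We will recruit at least 234 individuals to pilot the survey".

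**The concern.** The text gives a named formula, all four of its inputs and a result, so a reader can check it. Eight tasks per respondent should reduce the number of people needed about eightfold compared with one task each, and 234 looks too large for that. If the number does not follow, a published sample size is wrong as written or lacks an input. It also appears a second time as a recruitment target. What is at stake is whether the DCE calculation can be reproduced. No arm comparison in the trial depends on it.

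**Working it through.** **Inputs, all from the Discrete Choice Experiment subsection**
- Choice probability p = 0.33, so q = 0.67 (or p = 1/3, q = 2/3, since there are three options).
- Accuracy 90%, taken as allowable relative error a = 0.10. This is an assumption, because the article does not define the term.
- Confidence 95%, two-sided: z = 1.96, z² = 3.8416.
- Tasks per respondent r = 8.

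**Formula.** The article prints no equation. The usual form is the ordinary precision requirement for a proportion. With N choices the half-width of the confidence interval is z√(pq/N). Setting this equal to a·p gives N = z²q/(p a²) choices, and dividing by r gives respondents: n = z²q/(r p a²).

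**Attempt to reproduce 234**
- p = 0.33: 3.8416 × 0.67 / (8 × 0.33 × 0.01) = 2.5739 / 0.0264 = 97.5, so 98.
- p = 1/3: 3.8416 × 2 / (8 × 0.01) = 96.04, so 97.
- Ratio to the stated figure: 234 / 97.5 = 2.4.

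**Range over the reading of accuracy.** If 10% is an absolute error, N = z²pq/a² = 3.8416 × 0.2211 / 0.01 = 85 choices, and 85 / 8 = 10.6, so about 11 respondents. This is further from 234.

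**What would have to change to give 234, one input at a time**
- Tasks: 780 / 234 = 3.33 instead of 8, where 780 is N from the relative-error formula (3.8416 × 0.67 / 0.0033).
- Relative error: √(2.5739 / (8 × 0.33 × 234)) = √0.004167 = 0.0645, an accuracy of about 93.5%.
- Probability: q/p = 234 × 8 × 0.01 / 3.8416 = 4.87, so p = 0.17.

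None of these values is stated, and 33% is tied to the three options.

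**Allowing for non-response.** Dividing 97.5 by 0.30 gives 325, not 234.

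**Possible origins.** Two other routes land on or near 234:
- 780 choices × 0.30 = 234. This omits the division by eight tasks and multiplies by the response rate.
- An absolute-error formula with an added 90% power term, no division by tasks and p = 1/3: (2/9) × (1.96 + 1.2816)² / 0.01 = 233.5.

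Neither is the named formula with the stated inputs.

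**Main survey.** 5000 × 0.30 = 1500 expected responses, above both 98 and 234.

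**The case against.** The strongest objection is that the equation is not in the article and the accuracy level is undefined, so 98 depends on a supplied formula and a chosen reading. This stands in part. The 98 is conditional and must be labelled so, which is why the absolute-error result of 11 is shown beside it. It does not rescue 234, because neither reading of the stated inputs reaches that number. An unstated inflation is possible, but the sentence reads as a complete derivation and mentions none.

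Three stronger inferences are tempting, and the article does not support them.

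- A reader might conclude that 234 arose as 780 × 0.30. The match is close and 30% appears in the same subsection, but only in connection with the 5000 invitations. A second, unrelated route also comes to about 234. The origin is conjecture.
- A reader might say that the pilot target was copied from the wrong number, or that the pilot takes 136 people too many (234 − 98). The article gives no basis for the pilot size, and a pilot as large as the survey minimum may be deliberate. The formula sets a minimum for the survey and no requirement for the pilot, so there is no pilot figure to exceed. Setting the pilot at 98 would have no basis either.
- A reader might infer that a large pilot depletes the main survey. The article does not say whether pilot respondents come from the same people who are later invited.

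It is also fair to say that a minimum set too high does no harm to precision.

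**Conclusion.** The point holds as a reporting error: 234 is not the result of the named formula with the four stated inputs. Under the usual form with a 10% relative error the minimum is 98 (97 with p = 1/3), so the stated number is about 2.4 times too large; under an absolute error it would be about 11. The mismatch with 234 holds under both readings. The value 98 rests on the supplied formula and the relative-error reading.

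The consequence is small. The error is conservative, the planned mailing is expected to exceed either figure several times over, and neither the composite-outcome power simulation nor the power for individual outcomes uses the number. For the pilot, all that can be said is that it carries the same unexplained figure without a reason of its own.

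**What to change.** - Restate the survey minimum as 98 respondents (780 choices over eight tasks; 97 with p = 1/3), or keep 234 and state the different or additional input that produces it.
- Print the formula and say whether the 90% accuracy is a relative or an absolute error.
- Give the pilot size its own justification.
- Justify the main survey by the roughly 1500 expected responses and the subgroup analyses they are meant to support.

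The cost is a few edited sentences. The mailing, the survey design and the trial itself need not change.

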### Data monitoring

Data monitoring will be undertaken by the study management board. The study has no data monitoring committee as this is considered a low-risk study. This was discussed with the study Scientific Advisory Board who agreed with this approach.

### Adverse event reporting

As all patients’ care is managed by their usual diabetes care teams and the iDiabetes platform only generates treatment recommendations, there will be no adverse event reporting.

### Patient and public involvement

A PPI group was formed specifically for this study, consisting of patients and family members recruited from the NHS Scotland Diabetes Research Register and via social media outreach. The PPI group was consulted on all aspects of the project including shaping the study concept prior to funding application. Subsequently, two representatives were invited from the group as the study’s coapplicants for funding and ethics application and are part of the Study Management Board. Further regular meetings were organised via remote video conference to seek feedback from the PPI group on the study design and patient-facing materials including participant information sheets and recommendation outputs, which will be viewed by the patients on the MDMW patient interface as well as study website content (see figure 4). Additional patient feedback will be sought as part of the analysis of the platform, described in the qualitative analysis section above.

**Figure 4 F4:**
[figure not shown]
An overview and timeline of the PPI activities conducted throughout the iDiabetes study process. CSO, Chief Scientist Office

## Ethical considerations and dissemination plan

### Consent

#### iDiabetes study consent

Consent to take part in the study will take place at a cluster level on randomisation to an iDiabetes platform arm (*iDiabetes (guideline support*) or *iDiabetesPlus*). Patients will be sent information about the iDiabetes study if their primary care GP is randomised to the *iDiabetes (guideline support*) or *iDiabetesPlus* arm. Patients will not be required to consent individually. Patients who are registered with a primary care GP randomised to an iDiabetes platform arm will be given the opportunity to opt out of the study at an individual level at any point throughout the study period. This can be done when they attend their annual diabetes review. This approach was deemed acceptable by both the iDiabetes PPI group and the NHS Research Ethics Committee (REC) on the grounds that the study intervention was in the form of treatment recommendations, *not* direct changes to treatment and that these recommendations are based on international diabetes guidelines on the standard of care.

#### Genetic testing consent

To comply with the requirements of the Human Tissue Act 2004, explicit individual patient verbal consent for genetic testing will be obtained from the patients registered with primary care GPs randomised to the *iDiabetesPlus* arm prior to genotyping. This will take the form of the question ‘*Do you agree to your blood sample undergoing genetic analysis as part of iDiabetes and for future clinical care?’*, with the answer recorded in the SCI-Diabetes system by the person taking the blood test. Patients who do not wish to undergo genetic testing can still take part in the *iDiabetesPlus* arm without this aspect.

#### Echocardiography consent

For iDiabetesPlus patients with a pro-BNP 400 to 2000 pg/mL, further evaluation for heart failure will be performed using AI-assisted echocardiography using US2Ai echocardiography software. An additional PIS will be sent and informed consent obtained for patients prior to undergoing US2Ai echocardiography. For those who do not wish to consent they will be offered a routine NHS echocardiography appointment.

#### Qualitative study consent

Additional informed consent will be taken from participants who are invited to participate in semistructured interviews as part of the qualitative studies.

#### Health economics study consent

Informed consent will be taken from participants prior to the think-aloud interviews and DCE survey.

See online supplemental file 2 for consent documents.

### Research ethics Committee approval

This study was reviewed by the NHS Health Research Authority and given a favourable opinion by the East of Scotland Research Ethics Committee (REC reference: 23/ES/0008).

### Confidentiality

The study team will uphold the requirements of legal regulations such as the General Data Protection Regulation (EU) 2016/679 (GDPR), the UK Data Protection Act 2018 and the NHS Scotland Code of Practice on Protecting Participant Confidentiality when conducting the study. Published results will not contain any personal data that could allow identification of individual participants.

### Dissemination plan

The criteria for authorship will follow the criteria of the International Committee of Medical Journal Editors. Study findings will be published with the intention to submit a manuscript for publication no later than 12 months after the end of the study. Planned dissemination includes the following manuscripts: the main iDiabetes quantitative finding, iDiabetes qualitative analysis, iDiabetes cost-effectiveness analysis and iDiabetes DCE. Additional manuscripts may be prepared on aspects of the statistical analysis, technical development of the iDiabetes platform and ancillary outcomes. Study findings will also be submitted as abstracts to be presented at relevant scientific conferences.

A newsletter giving a summary of the results of the study will be made available to patients on the study website. There will be involvement with local and social media so patients with diabetes in Tayside are aware of the initiative and what it delivers.

### Access to data and amendments

Study-related monitoring, audits, REC review and regulatory inspection will be permitted. In the event of an audit, the Sponsor, representatives of the Sponsor or regulatory authorities will be given direct access to all study records.

Individual-level patient data will not be made publicly available due to data privacy/GDPR regulations. Additional access to the final study dataset on the Health Informatics Centre Trusted Research Environment (University of Dundee) will be approved by the chief investigator with an appropriate data-sharing agreement in place.

Amendments to the protocol will not be implemented without approval from the Sponsor and subsequent approval from the appropriate REC and NHS Research & Development Office. Any major amendments undertaken between the publication of the study protocol and the end of the study will be made explicit in the final published study report.

### Poststudy care

All diabetes care will be provided by the patients’ diabetes care team throughout the study with recommendations provided by iDiabetes platform. Following the end of the study, no further recommendations will be made by iDiabetes.

## Data Availability

No data are available.
